### Outcome variables

The main outcome variable will be tobacco use (Yes/No, defined as active use in the last 7 days)^25^ at the various time points. Abstinence validation will be performed with CO-oximetry on the day of surgery and at 12 months for subjects who declare themselves abstinent (patients with CO >6 ppm will be considered as active smokers)^26^. At the other time points (start of the study, and at 1, 3, 6 and 12 months) abstinence will be self-reported by the patient. The following secondary variables will be recorded at each assessment: 1) type of tobacco product (cigarettes, rolling tobacco, cigars, etc.); 2) pattern of consumption of each type of tobacco product (daily or occasional, and daily/weekly amount); and 3) level of nicotine dependence, using the Fagerström test (low 0–3, medium 4–6, and high 7–10)^27^. Other variables that will be assessed include motivation and self-efficacy, willingness to quit smoking according to the Prochaska and Di Clemente model^28^, level of motivation using the Richmond test^29^; and the General self-efficacy scale (based on Bandura’s social cognitive theory)^30^.

Another outcome variable will be surgical complications classified into the following groups and assessed on the day of surgery, on discharge from recovery-room care, hospital discharge, and up to 90 days post-surgery: 1) respiratory complications (bronchospasm, respiratory failure requiring oxygen and active treatment, respiratory superinfection requiring antimicrobial treatment, pleural effusion, other); 2) cardiovascular complications (deep venous and pulmonary thromboembolic disease, hypertensive crises, angina, new onset arrhythmias/blockages, acute myocardial infarction, heart failure, other); 3) postoperative complications of the surgical wound (dehiscence, fistula or infection of the internal or deep wound, seroma, wall abscess or fistula of the external wound with antimicrobial treatment and positive cultures, other); and 4) mortality (during hospitalization and within 90 days of surgery). All complications after the day of surgery will be recorded taking into account data from the patient’s medical history. Variables related to surgery: surgical time, blood transfusions (to be assessed as possible confounding variables for post-surgical complications and mortality). Variables related to hospital care: length of hospital admission (in days); and readmissions required within 12 months of hospital discharge.

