### Procedure

This pragmatic intervention will be carried out at different hospital services and will involve healthcare professionals from different ambits for evaluation. The intervention will begin in the pre-surgical period, at the pre-anesthetic visit, where smokers who meet the inclusion criteria outlined in the protocol will be invited to participate. Those who agree will receive more detailed explanations of the nature of the study and they will be asked to provide written informed consent. An information leaflet (see Supplementary file) will be provided to all patients who agree to take part. Within 24–48 hours they will receive a telephone call during which baseline data will be recorded, and at the end of the interview, patients will be randomly assigned to the IG or the CG. Participants will receive the following, according to their group.

*Intervention group (IG)*

Intensive intervention consisting of two pre-surgical visits starting at least four weeks before surgery (depending on the type of surgery) + an information leaflet (see Supplementary file) + pharmacological therapy (NRT if needed) + four follow-up consultations by telephone, carried out by expert staff trained in intensive smoking interventions (at 1, 3, 6 and 12 months after surgery) with the aim of maintaining abstinence.

*Control group*

A single visit with brief advice to stop smoking and the same information leaflet between three and six weeks before surgery (depending on the type of surgery) provided by healthcare personnel. Follow-up after discharge will be by telephone at 1, 3, 6 and 12 months after discharge, but no more advice will be given.

The intervention procedure is detailed in Figure 1.

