### Components of the intensive intervention

The intervention is based on the recommendations of smoking cessation treatment guidelines^15,31.^ The intervention aims to ensure that the patient stops smoking before surgery and remains abstinent for as long as possible. It comprises an initial face-to-face visit lasting between 30 to 45 minutes approximately four weeks prior to surgery, and a second telephone visit approximately two weeks prior to surgery. After surgery, patients will be followed up by telephone, with visits after 1, 3, 6 and 12 months. The professionals who will carry out the intervention are experts in the treatment of tobacco addiction and are members of the Preventive Medicine service of the hospital. The components of the various visits are detailed in Table 2.

**Table 2 t0002:** Components of intensive intervention visits in the RCT at the Vall d’Hebron University Hospital, Barcelona (N=232)

*Visits*	*Components*
**First visit** Face-to-face	Assessment of nicotine dependence (Fagerström test). Assessment of stage of change (Prochaska and DiClemente). Assessment of motivation (Richmond test). Assessment of general self-efficacy. Establishment of a plan to quit smoking, emphasizing the benefits of the upcoming surgery. If possible, setting a date to quit, ‘D’ day (try to make it as soon as possible before surgery). Prediction of difficulties that may arise, particularly the first few weeks, including symptoms of nicotine withdrawal syndrome. Recommendation of the use of pharmacological therapy (NRT) if necessary, except when contraindicated. Offer practical advice for problem solving/skills training, learning cognitive and behavioral activities to cope with the desire to smoke. Discussion of difficulties/triggers and how the patient can overcome them (avoiding triggers, changing routines). Description of previous experiences, discussion of what helped and what did not, build on success. Facilitate clinical support throughout the process. Agree on follow-up.
**Second visit** By phone prior to surgery	Assessment of self-reported abstinence. Reinforcement of abstinence before surgery. Assessment of difficulties and problems. Reinforcement of behavioral coping skills and social support. Assessment of adherence to drug treatment and any necessary changes. Recommendation of relapse prevention strategies for patients who remain abstinent. Offer of congratulations emphasizing the benefits of upcoming surgery. Arrangement of follow-up.

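### The 12-month abstinence endpoint relies on a CO reading that no described contact can supply, and the only written scoring rule leaves an unmeasured claim resting on self-report

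*Protocol article*

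**What the plan says.** All references are to the protocol article.

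- **Endpoint (Outcome variables).** "The main outcome variable will be tobacco use (Yes/No, defined as active use in the last 7 days".
- **Validation (Outcome variables).** Abstinence is to be checked by CO-oximetry at surgery and "at 12 months for subjects who declare themselves abstinent (patients with CO >6 ppm will be considered as active smokers". No other rule about a reading is given.
- **Self-report (Outcome variables, next sentence).** For what it introduces as the remaining time points, the article lists "start of the study, and at 1, 3, 6 and 12 months) abstinence will be self-reported by the patient". Twelve months therefore appears on both lists.
- **12-month contact, intervention group (Procedure).** "four follow-up consultations by telephone, carried out by expert staff trained in intensive smoking interventions (at 1, 3, 6 and 12 months after surgery". Components of the intensive intervention repeats this: "After surgery, patients will be followed up by telephone, with visits after 1, 3, 6 and 12 months".
- **12-month contact, control group (Procedure).** "Follow-up after discharge will be by telephone at 1, 3, 6 and 12 months after discharge".
- **Table 1** marks CO-oximetry on the day of surgery and at no other time.
- **Table 2**, which covers the intensive intervention only, lists an end-of-study CO measurement inside the row for telephone follow-up after surgery.
- **Discussion** expects CO readings at the end of the study as well as on the day of surgery.
- **Data analysis** commits to intention to treat. That does not say how a patient who claims abstinence but has no reading is classified.

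Figure 1, which details the procedure, is not shown in the text available.

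**The concern.** Exhaled CO cannot be measured over the telephone. A patient who reports abstinence on the 12-month call must therefore attend in person, and no such attendance is described for either arm in the text shown. Some missing readings are foreseeable, and they fall on exactly the patients whose status the reading is meant to settle.

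The written rule works in one direction only: a reading above 6 ppm overturns a claim. With 12 months also listed as self-reported, a literal reader would leave an unmeasured claim standing.

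Three features make this matter:

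- Twelve-month abstinence is the quantity behind the sample size and the one-year NNT.
- The Sample size and randomization section lists surgeons, collaborating researchers and outcome analysts as blinded, but not patients.
- In the intervention group the 12-month call is itself a consultation by smoking-cessation staff, whereas controls receive no further advice. Over-reporting could differ between arms, and CO is the safeguard against that.

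**Working it through.** **Inputs from the article.** Abstinence at 12 months 20% (intervention, IG) v 5% (control, CG); 58 per group in four groups, so 116 per arm; 10% loss, so 116 × 0.9 ≈ 104 evaluable per arm; α = 0.05. Power and sidedness are not stated. The rates of non-measurement and misreporting used below are assumptions; the article gives neither.

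**Plan's own figure.** Without a stated power, 232 cannot be strictly reproduced. Assuming two-sided α = 0.05, 90% power and pooled variance for IG v CG overall:

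n = [1.96·√(2 × 0.125 × 0.875) + 1.2816·√(0.20 × 0.80 + 0.05 × 0.95)]² / 0.15² ≈ 100.1, so 101 per arm; 101/0.9 gives 113; total 226, within 3% of 232. At 104 evaluable per arm, power is 91%.

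**Patients affected.** At the planned rates, 116 × 0.20 ≈ 23 IG and 116 × 0.05 ≈ 6 CG patients declare abstinence and need a reading.

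**Step 1: the scoring choice alone.** Take 20% v 5% as declared rates and assume 30% of declared abstainers in each arm are unmeasured, with no claim overturned among those measured.

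- Unmeasured scored as abstinent: 20% − 5% = 15 points; NNT = 1/0.15 = 6.7.
- Unmeasured scored as smokers: 0.20 × 0.7 − 0.05 × 0.7 = 14% − 3.5% = 10.5 points; NNT = 1/0.105 = 9.5.

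The gap of 4.5 points compares with a standard error of √[(0.16 + 0.0475)/116] = 4.2 points.

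**Step 2: direction of bias if unmeasured claims stand.** Now take 20% v 5% as true rates. Let f be the share of true smokers who claim abstinence and m the share of declared abstainers without a reading. Scored rates are 0.20 + 0.80·f(IG)·m and 0.05 + 0.95·f(CG)·m.

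| f (IG / CG) | m | IG | CG | Difference (points) | NNT | Chance of significance, 104 per arm |
|---|---|---|---|---|---|---|
| any | 0 | 20% | 5% | 15.0 | 6.7 | 91% |
| 5% / 5% | 50% | 22.0% | 7.4% | 14.6 | 6.8 | 85% |
| 5% / 5% | 100% | 24.0% | 9.75% | 14.25 | 7.0 | 79% |
| 10% / 5% | 50% | 24.0% | 7.4% | 16.6 | 6.0 | 91.5% |
| 10% / 5% | 100% | 28.0% | 9.75% | 18.25 | 5.5 | 92.5% |

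With no true effect (5% v 5%) and f = 10% / 5%, scored rates are 9.75% v 7.4% at m = 50% and 14.5% v 9.75% at m = 100%. The chance of a false significant result favouring IG is then about 9% and 18%, against a nominal 2.5%.

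**Step 3: cost of scoring unmeasured claims as smoking.** Scored rates are 0.20·(1 − m) and 0.05·(1 − m), again with 104 per arm.

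- m = 25%: 15% v 3.75%, 11.25 points, power 80%.
- m = 50%: 10% v 2.5%, 7.5 points, power 61%.

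**The case against.** **An unmeasured claim is never expressly called a success.** A reader might infer that the plan counts every unmeasured declared abstainer as abstinent. No sentence says that. The 6 ppm statement can be read as a cut-off rather than a full scoring rule, and listing 12 months under self-report could simply mean that the claim is made first and validated afterwards. This stands as a limit on the wording. It does not remove the problem, because the self-report sentence is presented as covering the time points without CO, and nothing else in the article overturns a claim.

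**Missing-reading rules usually sit in the full protocol or analysis plan.** True, and silence alone would be no finding. What is at issue is what the article does state: conflicting accounts of how its main endpoint is ascertained, together with a rule that works in one direction.

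**A reading is clearly intended.** Table 2 and the Discussion both expect it, Table 2 also foresees following up patients who do not attend, and Figure 1 is not visible. A reader should therefore not conclude that no 12-month reading is planned. But Table 2 puts it in a telephone row for one arm, and no control-arm attendance is described.

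**The bias need not favour the intervention.** It is tempting to say that unverified claims inflate the effect. That follows if a fixed share of declared abstainers is false in each arm: a 20% share implies that 0.05/0.80 ≈ 6.3% of IG smokers but only 0.0125/0.95 ≈ 1.3% of CG smokers misreport. If equal shares of smokers misreport, the difference shrinks slightly and power falls. The documents do not settle which applies, so this objection stands in full.

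**Step 1 compares two conventions and does not measure bias.** Also correct: if the unmeasured patients are truly abstinent, 10.5 points is the wrong figure. The comparison shows how far the result depends on an unfixed choice.

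**Conclusion.** The concern holds as a contradiction in how 12-month abstinence is ascertained, combined with a one-sided reclassification rule. As described, neither arm has a contact that yields the reading, and on a literal reading an unmeasured claim rests on self-report.

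The primary result and the NNT then depend on claims that may be unverified. With an assumed 30% unmeasured, the scoring choice is worth 4.5 points, slightly more than one standard error. Unverified claims would inflate the difference if false claims are more frequent among intervention-arm smokers. They would dilute it slightly, and cost power, if equally frequent among smokers in both arms.

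The documents do not support the stronger statements that the plan expressly scores unmeasured patients as successes or that the error must favour the intervention. All sizes rest on assumed non-measurement and misreporting rates. The contradiction itself rests on the text alone.

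**What to change.** 1. Reconcile Table 1, Outcome variables, Procedure, Components of the intensive intervention and Table 2. State that the 12-month CO reading already planned is taken in person from declared abstainers in both arms, in the same way, and remove 12 months from the list of time points that rest on self-report alone.
2. Define 12-month abstinence as no use in the last 7 days plus a recorded CO of 6 ppm or less. In the primary analysis, score a declared abstainer without a reading as a smoker.
3. Report the number of declared abstainers without a reading, by arm.
4. Give the analysis with unmeasured claims scored as abstinent as a sensitivity analysis.

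**Cost.** The wording is short, but the in-person contact is a real addition to the schedule as described: about 23 + 6 = 29 patients at the planned rates, including controls for whom no visit is described. Abstinence rates will look less favourable, and power falls if many are unmeasured: about 80% at 25% and 61% at 50%, with 104 evaluable per arm. The strict rule also brings its own bias if attendance differs between arms, which is why items 3 and 4 are needed. The article reports 25 subjects recruited at the time of writing. The rule should be fixed before 12-month data are analysed, since a choice made afterwards would be hard to defend.

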### Independent variables

The main independent variable will be ‘implementation of an intensive pre-surgical intervention to stop smoking’ (Yes/No). In addition, the following data will be recorded:

Sociodemographic variables such as sex, age, marital status, living with a smoker, education level, type of surgery.Comorbidities.Pharmacological treatment: none/NRT according to the recommendations of the different guidelines^15,31^.

The variables to be recorded and the frequency of recording are detailed in Table 1.

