**Follow-up visits** By phone after surgery	Assessment of self-reported abstinence. Assessment of treatment adherence and difficulties in following it. Reinforcement of behavioral strategies to cope with smoking urges. Relapse prevention. Recording data on tobacco use and variables if the patient continues to smoke. Measurement of CO-oximetry at the end of the study. Prompt notification of patients who do not attend, so as to try to arrange visits as soon as possible.

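### The article describes 12-month abstinence, the endpoint used for the sample size, as both CO-validated and self-reported; Table 1 marks neither measure at 12 months, and no CO step is given for controls

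*Protocol article*

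**What the plan says.** Sample size and randomization fixes the planning contrast as abstinence at twelve months, 20% in the intervention group and 5% in the control group, with 232 patients and 10% loss. The outcome is tobacco use in the previous 7 days.

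On how that outcome is ascertained, the article says the following.

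- **Outcome variables, validation sentence:** "Abstinence validation will be performed with CO-oximetry on the day of surgery and at 12 months for subjects who declare themselves abstinent", with the rule that "patients with CO >6 ppm will be considered as active smokers".
- **Outcome variables, next sentence:** "At the other time points (start of the study, and at 1, 3, 6 and 12 months) abstinence will be self-reported by the patient".
- **Independent variables:** "The variables to be recorded and the frequency of recording are detailed in Table 1".
- **Table 1:** the smoking status row is marked at baseline, day of surgery and 1 month, and is blank at 3, 6 and 12 months. The CO-oximetry row is marked on the day of surgery only.
- **Table 2**, titled "Components of intensive intervention visits in the RCT": under the post-surgery follow-up visits, which are by phone, it lists "Measurement of CO-oximetry at the end of the study".
- **Procedure, Control group:** "Follow-up after discharge will be by telephone at 1, 3, 6 and 12 months after discharge, but no more advice will be given".
- **Discussion:** refers to CO readings from the day of surgery and the end of the study, with no restriction to an arm.

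**The concern.** The first two statements assign 12 months to both classes. If the other time points are those without validation, 12 months cannot be among them. Table 1 should settle the matter but schedules neither the status nor its validation at 12 months. The only visit-level mention of end-of-study CO is in a table about the intervention arm, within telephone contacts at which the article does not say how CO would be measured.

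The primary comparison depends on which part staff follow. If CO is not collected, the endpoint is unverified self-report. Participants are not among those listed as blinded, and one arm has been counselled repeatedly to abstain. If CO is collected in the intervention arm only, claimed abstainers there can be reclassified as smokers while those in the control arm cannot, which works against the intervention.

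**Working it through.** **1. The wording and the tables side by side**

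| Source | 12-month smoking status | 12-month CO | Arm |
|---|---|---|---|
| Outcome variables, validation sentence | declared by the patient | yes, in claimed abstainers | not restricted |
| Outcome variables, next sentence | self-report | listed among the points without it | not restricted |
| Table 1 | not marked | not marked | all patients |
| Table 2 | self-report | yes, end of study | intervention visits |
| Control group procedure | telephone contact | not mentioned | control |
| Discussion | – | yes, end of study | not restricted |

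Several Table 1 rows carry marks at 3, 6 and 12 months that apply only if the patient smokes. They presuppose a status that the same table does not schedule at those visits. Because neighbouring rows keep their marks through to 12 months, damage in text extraction is an unlikely explanation for the blanks.

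**2. The planned sample size**

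No power is stated, so 232 cannot be reproduced from the article's inputs alone. Assume 90% power, two-sided 0.05, the pooled formula and the surgery types combined:

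n = [1.96·√(2 × 0.125 × 0.875) + 1.2816·√(0.20 × 0.80 + 0.05 × 0.95)]² / 0.15² = 1.5005² / 0.0225 = 100.1, so 101 per arm.

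After 10% loss: 101/0.9 = 112.2, so 113 per arm and 226 in total, within 3% of 232. This shows only that a two-arm, 12-month abstinence contrast is a plausible basis for the stated number.

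**3. Cost of CO in one arm instead of both**

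Inputs: 232 × 0.9 / 2 = 104.4, taken as 104 evaluable per arm (surgery types combined). Claimed abstinence is assumed equal to the planning rates, 20% and 5%. A share f of claimed abstainers is assumed to fail CO; the documents give no value, so a range is shown. Power is the exact probability that the uncorrected two-sided chi-square test rejects at 0.05.

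- CO in both arms: 0.20(1 − f) v 0.05(1 − f)
- CO in the intervention arm only: 0.20(1 − f) v 0.05

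| f | Both arms | Power | Intervention only | Power |
|---|---|---|---|---|
| 0 | 20% v 5% | 0.931 | 20% v 5% | 0.931 |
| 10% | 18% v 4.5% | 0.901 | 18% v 5% | 0.867 |
| 20% | 16% v 4% | 0.860 | 16% v 5% | 0.767 |
| 40% | 12% v 3% | 0.730 | 12% v 5% | 0.456 |

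At f = 20%, unequal collection costs 1 percentage point of difference (12 to 11) and about 9 points of power.

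**4. Self-report only**

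Assume true rates of 20% v 5% and a share g of continuing smokers who claim abstinence (again not in the documents).

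- Same g in both arms: the difference is 0.15(1 − g), which is 14.7, 14.3 and 13.5 points for g = 2%, 5% and 10%.
- g in the intervention arm only: 0.80 × g is added, which is 1.6, 4 and 8 points of spurious effect.

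The size and even the direction of the distortion therefore depend on who over-reports, which self-report cannot reveal.

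**The case against.** The best defence is that the intention is clear: status is self-reported at every contact and confirmed by CO at two of them, so the second 12 is a slip and Table 1 lacks a few marks. CO at 12 months or study end is stated in Outcome variables, Table 2 and the Discussion. The objectives compare the groups at 12 months, and the conditional rows of Table 1 cannot be completed without knowing who smokes. Table 2 also mentions patients who do not attend, which hints at some attendance in person. Figure 1 and the full protocol are not shown, and an article need not give every logistic detail.

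Much of this stands, and it rules out several stronger readings.

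- A reader might infer that the plan confines CO to the intervention arm. It does not: the validation sentence and the Discussion are neutral by arm, Table 2 by its title could not list a control procedure, and Table 1 marks 12-month CO for nobody. What is supportable is that no control-arm CO step is given.
- A reader might infer that the 12-month endpoint is not planned at all. The text does plan it; the schedule omits it.
- A reader might attribute the whole fall from 0.931 to 0.767 to unequal CO. The proper comparator is CO in both arms, 0.860; the rest of the fall would occur under the remedy too.
- A reader might conclude that the mixed model must use self-report throughout. Data analysis does not say which status enters the model, and that choice can be left to the analysis plan.

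The defence does not remove the contradiction. Even on the charitable reading, the sentence is wrong as written and Table 1 disagrees with the text.

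**Conclusion.** The point holds as an internal contradiction about how the sample-size endpoint is measured, compounded by a recording schedule that omits it and by the absence of any stated CO step for controls. If the tables are followed, the validated 12-month endpoint may not be collected, or may be collected unequally between arms.

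The cost of unequal collection is modest if few claims fail (0.90 to 0.87 at 10%) and severe if many do (0.73 to 0.46 at 40%). These figures rest on assumed failure rates, on claimed abstinence at the planning rates and on combining the surgery types; they illustrate what is at stake and do not predict it. The finding itself rests on the wording and the table marks and needs none of them. It should be corrected before 12-month assessments accumulate, since a CO reading not taken at 12 months cannot be recovered.

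**What to change.** 1. State that the 12-month endpoint is 7-day abstinence, CO-verified by the same procedure in both arms.
2. In Outcome variables, limit the self-report-only sentence to the start of the study and months 1, 3 and 6.
3. In Table 1, mark smoking status at 3, 6 and 12 months and CO-oximetry at 12 months, for both groups.
4. Say in the Procedure text that self-declared abstainers in both arms attend for the 12-month CO reading, and reconcile this with the telephone-only descriptions.
5. Treat a claimed abstainer without a reading identically in both arms.

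The cost is a wording amendment, a check that the data-collection forms match it, and the attendances. Under the planning rates these number 116 × 0.20 + 116 × 0.05 = 23.2 + 5.8 = 29 people before loss to follow-up. The promised 12-month CO already implies them. No change to the longitudinal model is required.

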The primary outcome is tobacco use (Yes/No, defined as active use in the last 7 days) and the secondary outcome is the presence of surgical complications (classified into respiratory, cardiovascular, wound complications, and mortality).

The specific objectives are the following:

To compare the effectiveness of the intervention in terms of abstinence, patient evolution, motivation and the attempts to quit smoking between the patients in the IG and the CG undergoing one of the two types of surgery.To compare the length of hospital stay (in days) and the number of re-admissions between the IG and the CG according to type of surgery.To compare surgical and post-surgical complications and mortality rates between the IG and the CG up to 90 days post-surgery.To assess whether the intervention can be implemented in the health system in Spain.

These objectives will be analyzed by comparing the results obtained in the IG and CG at the following time points: before surgery (at the beginning of the study), on the day of surgery, and at 1, 3, 6 and 12 months post-surgery (Table 1).

**Table 1 t0001:** Plans for assessment and collection of different variables in surgical patients who participate in the RCT at the Vall d´Hebron University Hospital, Barcelona (N=232)

*Variables*	*Baseline*	*Day of* *surgery*	*1 month* *post-surgery*	*3 months* *post-surgery*	*6 months* *post-surgery*	*12 months* *post-surgery*	*Re-admission*
Sociodemographic data	x						
Specialty	x						
Type of SI	x						
Smoker (yes/no)	x	x	x				
Type of consumption	x						
Amount of consumption	x	x	x (if s)	x (if s)	x (if s)	x (if s)	
Fagerström test	x		x (if s)	x (if s)	x (if s)	x (if s)	
Stages of change	x		x (if s)	x (if s)	x (if s)	x (if s)	
Richmond test	x		x (if s)	x (if s)	x (if s)	x (if s)	
Previous abstinence	x						
Previous drugs	x						
Living with smoker	x						
Comorbidities	x						
General self-efficacy scale	x						
CO-oximetry		x					
ASA PS classification		x					
ATB prophylaxis		x					
Duration of surgery		x					
Blood transfusion		x					
SatO2 at start of surgery		x					
Complications of surgery		x					
Complications at time of recovery room care discharge after surgery		x					
Attempts to quit			x (if s)	x (if s)	x (if s)	x (if s)	
Decrease in consumption			x (if s)	x (if s)	x (if s)	x (if s)	
Pharmacological treatment			x	x	x	x	
Is lack of NRT funding a problem?			x	x	x	x	
Readmission (yes/no)							x
Reason for readmission							x
SSI							x

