Postoperative mortality							x

RCT: randomized clinical trial. SI: surgical intervention. ASA PS: American Society of Anesthesiologists physical status scale. ATB: antibiotic. SatO2: oxygen saturation. NRT: nicotine replacement therapy. SSI: surgical site infection. if s: if smokes.

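### Table 1, named as the recording schedule, does not match the 90-day complication and mortality outcome defined in the text

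*Protocol article*

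**What the plan says.** The Introduction names surgical complications as the secondary outcome and sets a specific objective: "To compare surgical and post-surgical complications and mortality rates between the IG and the CG up to 90 days post-surgery".

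The Outcome variables section defines four classes (respiratory, cardiovascular, surgical wound, mortality), to be "assessed on the day of surgery, on discharge from recovery-room care, hospital discharge, and up to 90 days post-surgery". Death is defined as "mortality (during hospitalization and within 90 days of surgery"). On the source of the data it adds: "All complications after the day of surgery will be recorded taking into account data from the patient’s medical history". None of this is limited to readmitted patients.

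The Independent variables section then gives Table 1 its authority: "The variables to be recorded and the frequency of recording are detailed in Table 1".

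Table 1 has seven columns: baseline, day of surgery, 1, 3, 6 and 12 months after surgery, and re-admission. Its two general complication rows, the later being "Complications at time of recovery room care discharge after surgery", are marked on the day of surgery only. The rows for readmission (yes/no), "Reason for readmission", SSI and "Postoperative mortality" are marked in the Re-admission column only.

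**The concern.** The same outcome has two recording rules. The text asks for every class of complication in every patient to day 90. The table stops general complication recording at the recovery room and attaches infection and death to re-admission. Staff who build or complete forms are referred to the table.

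If the forms follow the table, two things are at stake. The first is completeness: complications arising on the ward after the recovery room, within the index stay, would have no place to be entered. The second is comparability of the arms. Re-admission happens after randomisation and is itself compared between the arms under the specific objectives. If infection and death were recorded only in readmitted patients, a difference in re-admission could appear as a difference in infection or death. The Data analysis section plans Cox regression of complications and says all analyses are by intention to treat. That requires event status and follow-up to day 90 for every randomised patient.

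**Working it through.** The plan states no figure on this point, so the check compares the text with the table cell by cell.

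**1. Required recording against scheduled recording**

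| Required by Outcome variables | Place in Table 1 |
|---|---|
| Complications on the day of surgery | Row present, Day of surgery column |
| Complications at recovery-room discharge | Row present, Day of surgery column |
| Respiratory, at hospital discharge and to 90 days | No row, no column |
| Cardiovascular, at hospital discharge and to 90 days | No row, no column |
| Wound infection, at hospital discharge and to 90 days | SSI row, Re-admission column only |
| Other wound complications (dehiscence, seroma and so on), same times | No row, no column |
| Death in hospital and to 90 days | Row present, Re-admission column only |

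Of the four assessment times in the text, the table covers the first two and has no column for the last two.

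**2. Could the 3-month column serve as day 90?** Not as marked. The 3-month column carries only smoking consumption, dependence, stage of change, motivation, quit attempts, pharmacological treatment and the question on nicotine replacement funding. The 1-month column adds only smoking status. No complication or mortality row is marked in either.

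**3. Four patients followed through both rules**

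- Respiratory infection on the ward, discharged, not readmitted: counted by the text; no row in the table.
- Death during the index stay: counted by the text; the only mark in the table is under an event this patient cannot have.
- Wound infection treated without admission: counted by the text; recorded by the table only if the Re-admission column is completed for patients who were not readmitted.
- Readmitted within 90 days with a wound infection: counted by both.

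**4. Two readings of the Re-admission column**

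- *Completed only when a re-admission occurs.* SSI and death are then observed conditional on a post-randomisation event.
- *Completed for everyone as a review after discharge.* The selection problem for SSI and death goes away. The missing rows for respiratory, cardiovascular and non-infectious wound complications remain. So does the lack of a 90-day limit: the text counts readmissions for 12 months after discharge but complications for 90 days after surgery, and one column serves both.

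The table conflicts with the text on either reading. Only the first brings in the selection problem.

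**The case against.** The strongest reply is that the text already provides for capture. It names the medical history as the source for all complications after the day of surgery, and it does not depend on re-admission. This stands: the outcome as defined in the text is sound, and for the document as a whole it would be wrong to say that ward events or deaths have no source.

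Second, the Re-admission column contains a yes/no item for readmission. A no can be entered only if the column is completed for patients who were not readmitted, so it may be a review form for everyone. This is plausible and cannot be excluded.

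Third, Table 1 is incomplete elsewhere. It has no row for length of stay, does not mark CO-oximetry at 12 months, and does not mark smoking status at 3, 6 or 12 months, although the text requires all of these. Absence from the table is therefore weak evidence that an item will not be collected. The REDCap instruments mentioned under Data collection are not shown.

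A reader might go further and infer that complications and deaths will be recorded only in readmitted patients, so that the secondary outcome is biased or loses a definite amount of power. The documents do not support that. They do not show the forms, they name a data source independent of re-admission, and they give neither complication rates nor the share of events treated without admission.

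These replies limit the consequence. They do not remove the conflict, because the article itself points to Table 1 for what is recorded and how often.

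**Conclusion.** The point holds as an inconsistency between the schedule and the outcome definition, on the trial's named secondary outcome. Table 1 lacks two of the four assessment times in the text, lacks rows for respiratory, cardiovascular and non-infectious wound complications after the recovery room, and places SSI and death under Re-admission only.

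The harm is conditional. It arises if the forms follow the table rather than the text. The selection problem for SSI and death requires, in addition, that the Re-admission column is completed only for readmitted patients. Neither condition is established. The size of any undercount or bias cannot be calculated from the documents, and no figure is offered. A correction is still warranted, because two recording rules for one outcome leave the choice to whoever builds or fills in the forms.

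**What to change.** Reconcile Table 1 and the REDCap forms with the Outcome variables section:

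- Add hospital discharge and day 90 as recording points for all randomised patients in both arms.
- At each, record respiratory complications, cardiovascular complications, wound complications (infectious and other) and death from the medical record, whether or not the patient was readmitted.
- Keep the Re-admission column for readmission and its reason.
- Check patients already recruited against their records and complete any missing entries.

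The cost is an edit to one table and to the forms, plus a record review that the text already plans. No visit is added and treatment does not change. The Current status section reports 25 recruited of the planned 232 (25/232, about 11%), so the retrospective work was small when the article was written. If the forms already collect these items, only the table needs correcting.
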